### Sample size

Power calculation [25] was informed by existing evidence [11–13, 15], predominantly the EVRA trial [15]. EVRA showed a 95% success rate for ulcer healing at 24 weeks. We anticipated a more modest success rate because our exclusion criteria did not limit participants to those with new ulcers. In addition, TIRS has very limited existing evidence with reporting healing ranging from 83 to 100% [21, 23]. An 80% success rate was felt to be reasonable for both treatments in a non-inferiority trial. A cohort of 308 patients (154 per arm) was required to ensure that if the null hypothesis should be rejected, the limits of a two-sided 90% confidence interval would exclude a difference between the groups of more than 15%, with 90% power at 5% significance level.

Given that existing evidence for TIRS consists mainly of small case series with widely varying healing rates, we planned once the first 50 cases exited the trial (either healed or completed 6 months of follow-up) as a pilot to inform a further power calculation for both superiority and non-inferiority outcomes.

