## Administrative information

**Table Taba:** 

**Trial synopsis**	
**Title**	Axial ablation versus terminal interruption of the Reflux Source in venous ulcer management: a randomised controlled trial in venous ulcer management
**Public title**	AAVTIRS trial
**Medical condition under investigation**	Lower limb venous ulcers
**Purpose of trial**	To evaluate whether there is a clinically significant difference between axial ablation of varicose veins and peri-ulcer terminal interruption of the reflux source in promoting healing of lower limb venous ulcers.
**Primary objective**	To determine if the proportion of ulcers healed within 6 months of endovenous treatment differs between patients undergoing axial ablation of varicose veins or terminal interruption of the reflux source by peri-ulcer foam sclerotherapy.
**Secondary objectives**	To determine whether there is a significant advantage to either treatment, in a reduction in ulcer size, encouraging wound regeneration, and venous disease severity or a significant difference in patient-assessed quality of life, between the two interventions
**Trial design**	Prospective single-centre assessor-blinded randomised controlled trial
**Primary endpoint**	Proportion of ulcers healed within 6 months of intervention
**Secondary endpoints**	Absolute and relative reduction in ulcer size Time to ulcer healing BWAT score progression VCSS progression over time Change in Charing Cross Venous Ulcer Questionnaire score from treatment to completion of follow-up
**Sample size**	320 individual ulcers
**Summary of eligibility**	Patients with a leg ulcer, attributable to venous insufficiency, without any contraindication to compression or either of the comparator treatment modalities will be included.
**Screening process**	All patients with a venous ulcer attending a Leg Ulcer Centre Ireland—a dedicated venous ulcer assessment clinic in Roscommon University Hospital will be considered for enrolment.
**Randomisation**	Affected legs will be randomised in a 1:1 ratio to axial ablation or terminal interruption of the reflux source.
**Treatment**	Patients will be treated on the same day as randomisation according to their assignment to either group
**Follow-up**	Patients will be followed monthly for 6 months.
**End-of-study**	The trial will end when all patients have been enrolled and completed both treatment and 6-month follow-up.

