#### AA

I.Ultrasound guided micropuncture of the desired axial veinII.Placement of a 5 French-gauge sheathIII.Passage of the Clarivein™ device to the proximal end of the treatment areaIV.Activation of the device, followed by withdrawal at a rate of 1 mm/s, while simultaneously infusing Sotradecol.

Variations of these treatments are at the discretion of the treating surgeon as long as the above steps are met. After treatment, all patients will be placed in compression bandages. They will then be followed up monthly at the same site with changes of their compression bandages in between by their local public health nurse (PHN) weekly, or more frequently as needed. If at any follow-up visit, their ulcer is seen to have healed, the time at which it healed will be noted in weeks from intervention. At this point, they will have completed their follow-up and will exit the trial. Patients in whom the ulcer has not fully healed at 24 weeks will also exit the trial. In either case subsequent treatment will be at the discretion of the surgical team.

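### If the interim pilot is the first 50 ulcers to exit, its healing rate is biased upward; the protocol should define it as the first 50 randomised

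*Protocol article*

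**What the plan says.** The Sample size section assumes equal healing in the two arms: "An 80% success rate was felt to be reasonable for both treatments in a non-inferiority trial". It asks for 154 patients per arm so that "the limits of a two-sided 90% confidence interval would exclude a difference between the groups of more than 15" percentage points, "with 90% power at 5% significance level".

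Because evidence on TIRS is thin, it adds an interim step: "we planned once the first 50 cases exited the trial (either healed or completed 6 months of follow-up) as a pilot". The section gives the purpose of this step as follows: "to inform a further power calculation for both superiority and non-inferiority outcomes".

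Exit depends on outcome. Under Treatment regimen (AA), a patient whose ulcer is seen to have healed at a follow-up visit leaves the study: "At this point, they will have completed their follow-up and will exit the trial". For the rest: "Patients in whom the ulcer has not fully healed at 24 weeks will also exit the trial". Final follow-up repeats both rules. On visit frequency, the synopsis says: "Patients will be followed monthly for 6 months".

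The interim result has a stated consequence. Criteria for discontinuation lists, as a ground for ending the trial, an interim power calculation that calls for so many more participants that the trial could not finish in reasonable time.

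**The concern.** A fast-healing ulcer can exit at its first monthly visit. One that never heals stays until week 24. While recruitment continues, the first 50 exits in calendar order therefore contain too many fast healers, and the slower ulcers enrolled beside them are still in follow-up. The healed fraction in that set does not estimate the primary outcome, the proportion healed at 24 weeks. This is selection on the outcome, and averaging does not remove it.

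The pilot exists to test whether 80% was a sound assumption. A rate biased upward makes the binomial variance look smaller, so an equivalence or non-inferiority calculation asks for fewer patients than are needed. The case the pilot should catch, true healing below 80%, is the one it could miss.

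**Working it through.** **1. The plan's own figure.** For equivalence with true difference 0, margin 0.15, a two-sided 90% interval and 90% power:

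n per arm = 2p(1−p)(1.645 + 1.645)² / 0.15² = 2p(1−p) × 10.82 / 0.0225

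At p = 0.80 this is 0.32 × 10.82 / 0.0225 = 153.9, so 154 per arm and 308 in total. The plan's figure is reproduced.

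**2. Accrual.** Recruitment began on 21 July 2020 (Trial status). It was to end in the first quarter of 2022 (synopsis) or the first half of 2022 (Trial status), which is about 88.3 or 101.3 weeks. The target is 308 (Sample size) or 320 (synopsis). The implied range is 308/101.3 = 3.0 to 320/88.3 = 3.6 ulcers per week.

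**3. Simulation, true healing 80%.** Assumptions not in the protocol:
- Poisson accrual at a constant rate
- Weibull healing times scaled to 80% healed by week 24, with shape 1 (constant hazard), 1.5 or 2
- healing detected at the next 4-weekly visit

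Mean healed fraction among the first 50 exits, with the total equivalence N that it would give:

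| Ulcers per week | Shape 1 | Shape 1.5 | Shape 2 |
|---|---|---|---|
| 1.5 (assumed) | 86.1% (230) | 85.0% (246) | 84.1% (258) |
| 3.0 | 92.3% (138) | 89.8% (178) | 88.2% (202) |
| 3.6 | 94.9% (94) | 92.2% (140) | 89.8% (176) |

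At 1 per week the fraction is about 83–84%. Among the first 50 enrolled, all followed to exit, it is 80% in every setting, and N stays at 308.

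**4. True healing 70%.** The requirement is 2 × 0.70 × 0.30 × 10.82 / 0.0225 = 202 per arm. At 154 per arm:
- SE = √(0.42/154) = 0.0522
- power = 2Φ(0.15/0.0522 − 1.645) − 1 = 2Φ(1.227) − 1 = 0.78

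At the implied accrual the first 50 exits show about 80–89% healed. Entered in the formula, 80% gives 154 per arm and 89% gives 95. The pilot would report that 154 is enough when about 48 more per arm are needed.

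**5. Superiority.** Assume true rates of 85% and 70%, 90% power and two-sided 5%, using the normal approximation with pooled variance under the null. The total needed is 322. The first 50 exits (shape 1.5) show on average 92.7% v 83.4% at 3.0 per week and 94.1% v 86.4% at 3.6 per week. The difference shrinks from 15 points to 9.3 and 7.7, and N rises to about 504 and 612. If a fixed 10-point difference is used instead, a higher base rate lowers N: 784 at 80% v 70%, 590 at 88% v 78%.

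**The case against.** **The reading.** The sentence can be taken to mean that the look happens when the first 50 enrolled cases have all healed or completed 6 months. The bias is then zero. This is a fair reading and it stands as a possibility. But the sentence counts cases by exit, names healing as one form of exit, and never mentions enrolment order. A reader could equally infer that the design is certainly biased, and the text does not establish that either. What is established is a rule that permits both readings, one of them biased.

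**The loss of power.** A reader might infer that the trial would be cut and lose its power. Pilot rates of 90% or 95% give 87 or 46 per arm, and at true 80% healing those sizes have 59% or 12% power. The protocol does not support that inference. The pilot only informs a calculation, and no passage says N would be reduced. If N stays at 154 per arm and healing is 80%, power stays at 90%. The harm that needs no cut is the missed increase in step 4.

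**The direction.** It would also be too broad to say that the recalculated N must be too small. The protocol plans a superiority calculation as well, and on observed arm rates that one errs upward. The protocol does not say which inputs it would use, and Statistical analysis keeps allocation concealed at the interim with limited exceptions.

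**The size.** The implied accrual is an average over the whole recruitment period, and early accrual may have been slower. Healing-time shapes are assumed. This stands, and is why ranges are given. The bias was upward in every setting tried.

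**Conclusion.** The point holds conditionally. If the pilot is the first 50 ulcers to exit, its healing rate overstates 24-week healing. At true 80% the overstatement is about 8 to 15 points at 3.0–3.6 ulcers per week and about 3 to 4 points at 1 per week, given constant accrual and the healing-time shapes tried. If the first 50 enrolled are meant, all followed to exit, there is no bias.

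On the exit-order reading, the equivalence or non-inferiority calculation understates N and can hide a true rate below 80%. At 70%, the trial would continue at about 78% power with no warning. A superiority calculation on observed arm rates can overstate N, and so could wrongly meet the feasibility ground under Criteria for discontinuation. For equivalence the same bias makes that ground less likely to be met.

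This should be fixed. It is an ambiguity with a material consequence on one reading, not proof that the trial is underpowered.

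**What to change.** Replace the pilot definition with one sentence: the pilot is the first 50 ulcers randomised, analysed once all 50 have healed or reached 24 weeks. Alternatively, estimate 24-week healing by Kaplan-Meier from all ulcers enrolled by the interim date. In either case, use the pooled, treatment-blind rate to recompute the equivalence N, which also fits the concealment of allocation at the interim.

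If the look has already been taken on the first 50 exits, recompute it on this basis. Enrolment and exit dates with healing status are enough, and no new data are needed.

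The cost is small. With the first 50 randomised, the interim falls about 2 months later. The Kaplan-Meier version causes no delay. Neither removes sampling error: at 80% healing, 50 ulcers give a 95% half-width of 1.96 × √(0.80 × 0.20/50) = 0.11, so the recomputed N should be shown over that range.

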### Outcomes

#### Primary outcome

The primary outcome is the proportion of ulcers which have healed by the time they are reviewed at 24 weeks.

#### Secondary outcomes

The following are the secondary outcomes:Time to ulcer healing, in those ulcers where complete healing is achievedAbsolute reduction in ulcer sizeRelative reduction in ulcer size as a percentage of original ulcer areaWound regeneration as indicated by changes in Bates-Jensen Wound Assessment Tool (BWAT) score over timeChange in Venous Clinical Severity Score (VCSS) monthly from randomisation to exit from the studyChanges in Charing Cross Venous Ulcer Quesionnaire (CCVUQ) score from randomisation to exit from the study

The BWAT is a tool originally derived for assessing pressure ulcers [26], which has been validated for venous ulcer use [27].

The VCSS is an objective measure of the severity of venous disease, encompassing both ulceration and wound factors, as well as non-wound related signs and symptoms [28].

The CCVUQ is a quality of life questionnaire specific to venous leg ulcers [29].

### Safety

#### Definition of an adverse event

Any medical misadventure encountered as a direct or indirect result of treatment received as part of the trial.

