**Safety monitoring**	The principal investigator will be notified of any serious adverse events, and they will liaise with all investigators and the ethics committee.
**Criteria for stopping trial on safety grounds**	Unacceptable risk to participants due to unexpected serious adverse events Unacceptable rate of adverse events Interim demonstration of a significant difference in efficacy Interim demonstration of a significant difference in the rate of adverse or serious adverse events Intolerable discomfort during treatment or compression, or inability to adhere to the protocol for any other safety-related reason leading to insufficient compliance with randomisation
**Registration**	ClinicalTrials.gov registration NCT04484168. Registered on 23/7/2020
**Recruitment**	Commenced on 21 July 20—ongoing. Planned completion 1st quarter of 2022, last patient last visit 3rd quarter of 2022
**Recruiting country**	Ireland
**IPD sharing**	Not planned
**Funding**	No funding has been received for this research.
**Ethics**	Approved by the Galway University Hospitals Clinical Research Ethics Committee 18 June 2020, ref. no. C.A. 2416

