#### Definition of a serious adverse event

Any adverse event, as defined, that results in hospitalisation or prolonged hospital stay, permanent or prolonged incapacity, significant disruption to daily life, threat to life, death, or any congenital abnormality arising from treatment, will be deemed a serious adverse event.

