#### Anticipated adverse events

The procedures involved in this trial are typically safe and well tolerated. Though any serious adverse event is unlikely, there are known potential adverse events with both treatments. These include the following:PainBleedingInfectionPhlebitisStaining of skinPalpable subcutaneous lumpsNew ulcerationDeep vein thrombosisPulmonary embolism, including life-threatening or fatal embolismStrokeNerve injury leading to pain/paraesthesia/reduced sensationSkin breakdown or hypersensitivity reaction secondary to compression/dressingsAdverse or hypersensitivity reaction to local anaesthetic or Sotradecol

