#### Adverse event reporting

The principal investigator should be notified of all adverse events. In the event of multiple similar adverse events, or any serious adverse event, the trial monitoring committee and local ethics committee will be notified, and risk analysis is performed.

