### Trial monitoring

The principal investigator will take responsibility for the day-to-day management of the trial supervised by the supervising investigator. Meetings will be held every 2 weeks between the principal investigator and supervising investigator to monitor recruitment, data collection and problems as they arise. The trial monitoring committee will meet as necessary to review safety issues. An independent data monitoring committee has not been established as the trial interventions are low-risk and consist of already-available and recognised treatment strategies. Any safety or equipoise concerns will be reported to those members of the Department of Vascular Surgery in University Hospital Galway who are not involved in the conduct of the trial for their consideration. This will include the results of the interim analysis.

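### Adverse and serious adverse events are defined by a causal link to trial treatment, so the safety counts depend on a prior attribution that the protocol assigns to nobody

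*Protocol article*

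**What the plan says.** All references are to the protocol article.

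- **Definition of an adverse event:** "Any medical misadventure encountered as a direct or indirect result of treatment received as part of the trial". Causation by trial treatment is part of the definition.
- **Definition of a serious adverse event:** it opens with "Any adverse event, as defined, that results in hospitalisation or prolonged hospital stay" and goes on to list further outcomes, including death. The words *as defined* carry the causal condition over.
- **Adverse event reporting:** "The principal investigator should be notified of all adverse events". The duty covers adverse events in the defined sense. Serious events, and multiple similar events, also go to the trial monitoring committee and the ethics committee.
- **Trial synopsis, safety stopping criteria:** these include "Unacceptable rate of adverse events" and "Interim demonstration of a significant difference in the rate of adverse or serious adverse events". The later section Criteria for discontinuation omits both rate-based criteria, but its own safety criterion is also worded in terms of adverse events.
- **Trial monitoring:** "An independent data monitoring committee has not been established as the trial interventions are low-risk".

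No section provides for recording events whatever their cause, or for judging relatedness after an event has been recorded.

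**The concern.** When causation is part of the definition, the judgement about cause decides whether an event is counted at all. It should instead describe an event that has already been counted. Two things follow.

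1. **Loss of events.** An admission or death that is considered unrelated drops out of the safety data. Nobody can revisit the judgement later, for example if several such events gather in one arm.
2. **Possible bias between arms.** The two procedures differ in invasiveness (needle injection of foam versus a sheath and rotating-wire catheter). If the person judging cause knows which was given, the same event could be attributed more readily after one procedure than the other. The recorded rates would then differ without a true difference, or a true difference could be hidden.

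At stake are the safety comparison between the arms and the stopping criteria that use these counts. The primary endpoint, ulcer healing, is not affected.

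**Working it through.** **Step 1. Follow the definitions.** Suppose a participant is admitted to hospital and the admission is judged unrelated to treatment.

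- It fails the adverse-event definition, because it is not a result of trial treatment.
- It therefore fails the serious-event definition, although hospitalisation is on the outcome list.
- The notification rule then does not apply.
- It enters neither the overall adverse-event rate nor the between-arm comparison in the synopsis.

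The protocol does not say when cause is judged. Under its rules the judgement has to come first, because an event is not notifiable until it has been attributed.

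**Step 2. Is attribution a real decision here?** The section Anticipated adverse events says "there are known potential adverse events with both treatments", and its list includes infection, new ulceration, deep vein thrombosis and stroke. Such events can also occur in these patients without treatment, so assigning a cause is a matter of judgement.

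**Step 3. Sample sizes.** The Sample size section states "A cohort of 308 patients (154 per arm) was required". That figure reproduces as an equivalence calculation with 80% healing and a 15% margin:

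n per arm = 2 × 0.80 × 0.20 × (1.645 + 1.645)² / 0.15² = 0.32 × 10.82 / 0.0225 = 153.9, so 154 per arm and 308 in total.

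It is used below only as the end-of-trial size. The only interim look described follows the first 50 cases to exit, which is about 25 per arm under 1:1 allocation.

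**Step 4. Illustration (all rates assumed).** Take a true event rate of 20% in both arms, with 80% of events attributed in one arm and 50% in the other.

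- Recorded rates: 0.20 × 0.80 = 16% and 0.20 × 0.50 = 10%.
- Chance of a nominally significant difference (two-sided 5% z-test) = Φ[(d − 1.96·s₀)/s₁] + Φ[(−d − 1.96·s₀)/s₁], where d is the difference, s₀ the pooled and s₁ the unpooled standard error.
- At 154 per arm, s₀ = 0.0383 and s₁ = 0.0382. The first term is Φ(−0.396) = 0.346 and the second is negligible: **about 35%**.
- At 25 per arm, s₀ = 0.0951 and s₁ = 0.0947. The terms are Φ(−1.335) = 0.091 and Φ(−2.601) = 0.005: **about 10%**.
- Fisher's exact test, which the protocol also names, gives about 29% and **about 4%** by exact enumeration.

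**Step 5. Range over the assumptions** (z-test / Fisher):

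| True rate, both arms | Attribution | Recorded | 154 per arm | About 25 per arm |
|---|---|---|---|---|
| 10% | 90% v 70% | 9% v 7% | 10% / 7% | 6% / 0.6% |
| 10% | 80% v 50% | 8% v 5% | 19% / 13% | 7% / 0.5% |
| 20% | 90% v 70% | 18% v 14% | 16% / 12% | 7% / 3% |
| 20% | 80% v 50% | 16% v 10% | 35% / 29% | 10% / 4% |
| 30% | 90% v 70% | 27% v 21% | 23% / 20% | 8% / 4% |
| 30% | 80% v 50% | 24% v 15% | 51% / 46% | 12% / 7% |
| 20% | 80% v 80% | 16% v 16% | 5% / 3% | 5% / 2% |

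The last row is the control. With equal attribution the error rate is nominal or below, although 20% of events are still lost.

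**Step 6. The opposite direction.** A true difference of 20% versus 10% has about 69% power at 154 per arm (z-test). With 50% versus 90% attribution the recorded rates become 10% and 9%, and a difference is declared only about 6% of the time.

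**The case against.** Several points can fairly be made for the protocol.

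- **The filter is wide.** *Direct or indirect* is generous wording. Compression is part of trial treatment, and reactions to it are listed. Thrombosis, embolism and stroke are named as known risks of both treatments, so they are unlikely to be dismissed. This stands, and it limits how many events would be lost. The condition is still causal, and it applies to deaths and admissions outside that list.
- **Unattributed events may still be noted.** The case report form is not shown, and some wound and skin findings are recorded at every visit regardless of cause. This stands. A reader might infer that an unattributed event is never recorded anywhere. The text supports only that it need not be reported as an adverse or serious adverse event.
- **Biased attribution is not shown.** A reader might infer that the unblinded surgical team decides cause. No section says so. Adverse events go to the principal investigator, those who collect and analyse data are kept away when the envelope is opened, and follow-up assessment is by blinded nurses. This stands, so differential attribution is an assumption.
- **The stopping rule looks at an interim.** A reader might apply the 35% to it. At the only interim described, the same assumptions give about 10% or 4%. The larger figure belongs to an end-of-trial comparison.
- **There is other oversight.** A trial monitoring committee exists, and safety concerns go to department members not involved in the trial. This stands, but on the stated rule what must be reported to them has already passed the causal filter.
- **Safety is not a listed outcome.** This is correct, and the protocol states no aim of showing equal safety. It does make adverse-event rates a reason to stop.

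This is not detail left to a fuller document. The article states the definitions, and the definitions are what is at fault.

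**Conclusion.** The point holds as a defect in the stated definitions. Adverse and serious adverse events are both conditional on causation by trial treatment, notification follows the same definition, and the safety criteria in the synopsis and in Criteria for discontinuation therefore rest on a prior judgement that the protocol assigns to nobody. This conclusion needs no numerical assumption.

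The size is unknown, because the protocol gives neither event rates nor attribution rates. Over the unequal-attribution scenarios tabulated, the chance of a spurious significant difference by z-test is about 10% to 51% at 154 per arm and about 6% to 12% at about 25 per arm; Fisher's test gives lower values. All of this requires attribution to differ by arm, which the documents do not show. The documents therefore do not support a claim that the interim stopping rule is seriously distorted. Loss of events judged unrelated needs no such difference and can occur at any sample size.

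The change is worth making. It bears on the safety comparison and leaves the healing endpoint untouched.

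**What to change.** 1. Define an adverse event as any untoward medical occurrence after randomisation, whether or not it is related to treatment.
2. Keep the existing outcome list for serious adverse events, but without the causal condition.
3. Record relatedness as a separate field, and state who judges it; where possible this should be someone unaware of the allocation.
4. Tabulate all events and treatment-related events by arm, and say which count each safety criterion uses. The synopsis and Criteria for discontinuation should be reconciled on this, since only the synopsis has the rate-based criteria.

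The cost is protocol wording, one added field on the case report form, and a few more events to log at the monthly visits already planned. Treatment, follow-up and sample size do not change. Recruitment was already under way when the article was written, so events seen under the present definition should be reviewed for omissions as far as the records allow.
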